**Meningioma/glioma/others (cases)**			
**Maximum diameter of tumor (mm)**			
**Anesthesia duration (min)**			
**Surgery duration (min)**			
**Bleeding volume (mL)**			
**Urine volume (mL)**			
**Sodium lactate ringer injection (mL)**			
**Hydroxyethyl starch injection (mL)**			
**Concentrated red blood cells (U)**			
**Fentanyl dosage (mg)**			
**Rocuronium dosage (mg)**			
**Ephedrine dosage (mg)**			
**PEEP level (cmH**_**2**_**O)**			
**PEEP service time (min)**			

#### Withdrawal of research

Because participation in the trial will be voluntary, the patients will have the right to withdraw their consent to participate in the study at any time and for any reason without any further treatment. In addition, if the researcher believes that participation is not in the patient’s best interests, the researcher has the right to terminate his/her participation at any time. The reasons and circumstances for disenrolling from the study will be recorded in the case report form.

#### Reporting of adverse events

All adverse events will be treated immediately and monitored until stabilization or resolution. The chief investigator will be responsible for reporting the event immediately to the Endpoint Adjudication Committee. The severity and causality of the adverse events will be assessed and recorded. Compensation will be provided in accordance with the relevant national regulations in the event of test-related damage.

#### Data acquisition and management

All personal information will be collected through the hospitalized medical records and be kept strictly confidential for research purposes only. Only the primary investigator and the designated researcher can obtain interim results and final test data. The data monitoring of this study will be performed independently by a Data Monitoring Committee (DMC) composed of specialists in anesthesiology, ethics, statistics, and methodology. The progress of the study will be evaluated, and the accuracy and integrity of data records will be verified through regular interviews. At the end of the study, the original data and results will be submitted to the Scientific Research Management Committee and disclosed to the public after the study results are published. The study results will be published in peer-reviewed journals.

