#### Randomization

All participants who meet the inclusion criteria will be randomly divided into two groups, P6 group (PEEP = 6 cmH_2_O) or Pi group (individualized PEEP) in a ratio of 1:1. Randomization will be achieved using a computer-generated randomization table. The designated staff will perform the allocation sequence and assign participants to the interventions. This research staff will implement the distribution sequence through sealed and opaque envelopes. Participants will not open the corresponding envelopes until they have completed the experiment. The patients, surgeons, and staff involved in data collection and follow-up visits will be blinded to the grouping; however, the anesthesiologist responsible for the implementation of anesthesia will be aware of the grouping.

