#### Sample size estimation and interim analysis

The main outcome of this study is the incidence of pulmonary complications 1 week after surgery. In the pre-test (20 cases in each group), the incidence of pulmonary complications 1 week after surgery in the P6 and Pi groups was 24% and 13.5%, respectively. Using the PASS15.0 procedure with *α* = 0.05 and *β* = 0.2, the minimum sample size of each group was calculated to be 216 cases. Based on the shedding rate of 20%, the number of cases included in each group will be at least 216 ÷ (1–20%) = 270. A total of 540 patients will need to be enrolled in the two groups in this study. The first patient was enrolled on 1 September 2021. The expected duration of the study is 25 months.

There will be a formal interim analysis performed by the Data Monitoring Committee to evaluate the efficacy of the primary outcome once 50% of the planned patients have been randomized and initiated intervention and have been followed up until discharge. The *p* value for the analysis will be set at *p*<0.001 using the alpha-sparing technique (O'Brien-Fleming) for benefit or harm. Stoping rules for adverse events: we will consider patients withdrawal from the trial if the following conditions occur. (1) severe brain swelling during surgery; (2) persistent hypotension and circulatory instability. 

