#### Trial organization

The steering committee is composed of principal investigators who contributed to the design and approval of the final protocol (Additional file 2). The Executive Committee is composed of the main investigators and is responsible for the administration, trial, and data collection. The data management team is composed of external independent experts in anesthesiology, statistics, and imaging. It is responsible for checking the integrity and reliability of the data, and it will recommend the continuation or discontinuation of the trial according to the results of the interim analysis. The trial overseeing group is composed of a project manager and experts in methodology and ethics. It is responsible for monitoring recruitment rate, clinical intervention, and follow-up and arranging a research progress meeting with principal investigators every month.

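### The primary investigator may obtain interim results with about half the trial still to recruit, and the protocol article does not agree with itself on who sees and acts on them

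*Protocol article*

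**What the plan says.** Four sections of the protocol article bear on this.

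- **Data acquisition and management.** On access: "Only the primary investigator and the designated researcher can obtain interim results and final test data". No time limit follows. The next sentence gives data monitoring to an independent Data Monitoring Committee (DMC) with expertise in anesthesiology, ethics, statistics and methodology.
- **Sample size estimation and interim analysis.** "There will be a formal interim analysis performed by the Data Monitoring Committee to evaluate the efficacy of the primary outcome", to take place "once 50% of the planned patients have been randomized and initiated intervention and have been followed up until discharge". The threshold is p<0.001, for benefit or harm.
- **Statistics.** Each patient's data go to the DMC at hospital discharge, and the DMC's own data collector checks them.
- **Trial organization.** This section does not mention the DMC. It describes another body: "The data management team is composed of external independent experts in anesthesiology, statistics, and imaging". Of that body it says that "it will recommend the continuation or discontinuation of the trial according to the results of the interim analysis". On the investigators: "The Executive Committee is composed of the main investigators and is responsible for the administration, trial, and data collection".

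On blinding, the Randomization section says that "The patients, surgeons, and staff involved in data collection and follow-up visits will be blinded to the grouping". The anesthesiologist who gives the anesthetic knows the allocation.

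**The concern.** In a trial with an independent monitoring committee, comparative interim results normally stay with that committee, so that those who recruit and treat the remaining patients do not know which arm is ahead. The access sentence does the opposite: it opens interim results to the person leading the trial, and it sets no point before which they stay closed.

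This trial gives such knowledge some room to act. It has a single center and is single-blind. The main investigators administer it. Under Withdrawal of research, a researcher may end a patient's participation at any time on a judgement of that patient's interests. An investigator who knows the interim difference could, without intending to, recruit differently, let that knowledge affect co-management through the unblinded anesthesiologist, or reach withdrawal decisions differently. The analysis cannot remove such effects afterwards.

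The second difficulty is internal. The access rule, the interim-analysis section and the organization section do not together describe one workable flow from data to result to recommendation.

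**Working it through.** **1. Who does what, side by side**

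| Function | Who | Section |
|---|---|---|
| May obtain interim results | Primary investigator and designated researcher, exclusively | Data acquisition and management |
| Monitors data independently | DMC (anesthesiology, ethics, statistics, methodology) | Data acquisition and management |
| Receives and checks patient data | DMC | Statistics |
| Performs the interim analysis | DMC | Sample size estimation and interim analysis |
| Checks data; recommends continuing or stopping | Data management team (anesthesiology, statistics, imaging) | Trial organization |
| Takes the final decision | Not named | – |

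The access sentence can be read in two ways.

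- *Literally*, it shuts out both the body that runs the analysis and the body that must recommend on it. Neither could then do its job.
- *As a limit within the study staff*, the DMC keeps its access. The primary investigator may still obtain interim results mid-trial, which undercuts the independence claimed in the next sentence.

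The sentence needs changing on either reading. The two expert bodies share two specialties and differ in the others (ethics and methodology against imaging), so the text does not establish that they are one body under two names.

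**2. The plan's own sample size**

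Inputs from the sample size section: 24% and 13.5%, α = 0.05, power 80%. Allocation is 1:1. Sidedness is not stated; two-sided is assumed because it reproduces the figure.

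n = [z₁₋α/₂ √(2p̄(1−p̄)) + z₁₋β √(p₁(1−p₁)+p₂(1−p₂))]² / (p₁−p₂)²

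With p̄ = 0.1875: (1.960 × 0.5520 + 0.8416 × 0.5470)² / 0.105² = 215.7, so 216 per group. Then 216/0.8 = 270 per group and 540 in total. The stated figures reproduce.

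**3. Patients still to recruit at the interim**

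- Trigger: 0.5 × 540 = 270 patients followed to discharge.
- Recruitment window from Trial status: September 2021 to June 2023, about 22 months. Rate: 540/22 = 24.5 per month, or about 0.81 per day.
- Time to discharge is not given; 7 to 28 days is assumed. Patients randomized meanwhile: 0.81 × 7 ≈ 6 to 0.81 × 28 ≈ 23.
- Remaining: 270 − 6 = 264 to 270 − 23 = 247, which is 49% to 46% of 540.

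**4. Would the trial go on after the interim?**

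The chance of crossing two-sided p<0.001 at the planned rates is

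Φ{[0.105√n − 3.291 × 0.5520] / 0.5470}

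- n = 135 per arm (no losses): Φ(−1.09) = 0.138.
- n = 108 per arm (20% losses): Φ(−1.33) = 0.092.

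So with a probability of about 86% to 91% the boundary is not crossed and recruitment continues.

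No calculation from the document gives the size of any resulting bias.

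**The case against.** A fair defense has five parts.

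- **The DMC is not really excluded.** A reader might infer from the word 'only' that it is. It receives the data and runs the test, so it must have the result, and the sentence follows one on confidentiality of personal information. This stands: the practical problem is what the sentence allows the investigator, not what it denies the DMC.
- **There are not three rival decision-makers.** A reader might infer this from the three sections. They name three functions (access, analysis, recommendation), and nobody is named as taking the decision. The recommendation goes to external independent experts, not to investigators. This also stands. What remains is that the functions are not aligned and that the two bodies differ in name and composition.
- **Permission is not disclosure.** The text says that results can be obtained. It does not say that they will be, or when, or that they will be shown by arm. True, but the interim is a formal efficacy comparison and nothing restricts access to its result.
- **Outcome assessment is protected.** Follow-up staff are blinded, two blinded specialists read the radiographs, and only concordant readings count. An aggregate difference reveals no patient's allocation, so it does not by itself let a blinded assessor grade cough or dyspnea differently by arm. This largely stands, and it narrows the concern to enrolment, co-management and researcher-initiated withdrawal.
- **The article is condensed.** The full protocol is available separately and may be clearer. But the point rests on a rule that the article states, not on a detail that it leaves out.

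**Conclusion.** The point holds in limited form. The article permits the primary investigator and a designated researcher to obtain interim results while about 247 to 264 of 540 patients are still to be recruited, in a trial that would most likely continue past its interim. These figures assume even recruitment over about 22 months, 7 to 28 days to discharge, the planned event rates and a two-sided test. Separately, the sections on access, interim analysis and organization do not fit together.

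The document does not show that the investigator will see the results, that the DMC is barred from them, or that outcome grading would be biased by arm. The plausible routes are enrolment, co-management and withdrawal. Their effect cannot be quantified, and no sample size or error rate changes. The matter still deserves correction because knowledge of an interim difference cannot be withdrawn once it is shared, and the article reports the trial as recruiting.

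**What to change.** - In Data acquisition and management, state that comparative interim results go only to the DMC and its statistician. Until database lock the investigators are told only to continue or to stop; their own access is to final data.
- Reconcile that section, the interim-analysis section and Trial organization so that the DMC alone performs the interim analysis and makes the recommendation. Remove the recommending role from the data management team or, if it is the same body, use one name and one membership list.
- If the interim has already taken place, record who saw which results and when.

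The cost is an amendment to the wording. The DMC already exists and includes statistical expertise, so no new staff are needed, and neither the sample size nor the analysis changes.

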#### Sample size estimation and interim analysis

The main outcome of this study is the incidence of pulmonary complications 1 week after surgery. In the pre-test (20 cases in each group), the incidence of pulmonary complications 1 week after surgery in the P6 and Pi groups was 24% and 13.5%, respectively. Using the PASS15.0 procedure with *α* = 0.05 and *β* = 0.2, the minimum sample size of each group was calculated to be 216 cases. Based on the shedding rate of 20%, the number of cases included in each group will be at least 216 ÷ (1–20%) = 270. A total of 540 patients will need to be enrolled in the two groups in this study. The first patient was enrolled on 1 September 2021. The expected duration of the study is 25 months.

There will be a formal interim analysis performed by the Data Monitoring Committee to evaluate the efficacy of the primary outcome once 50% of the planned patients have been randomized and initiated intervention and have been followed up until discharge. The *p* value for the analysis will be set at *p*<0.001 using the alpha-sparing technique (O'Brien-Fleming) for benefit or harm. Stoping rules for adverse events: we will consider patients withdrawal from the trial if the following conditions occur. (1) severe brain swelling during surgery; (2) persistent hypotension and circulatory instability. 

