## Introduction

Postoperative pulmonary complications (PPCs) are common, with an incidence of 39% [1–3]. Miskovic et al. [4] broadly described PPCs as “complications affecting the respiratory system after anesthesia and surgery,” while most studies describe PPCs as atelectasis, pneumonia, pulmonary edema, exacerbation of underlying chronic lung disease, or postoperative respiratory failure [5]. Patients undergoing a craniotomy are exposed to intraoperative mechanical ventilation, postoperative bed rest, limb paralysis, and other factors for a long time, thus resulting in obstruction of sputum drainage, which significantly increases the risk for PPCs [6, 7]. In addition, a postoperative state of low consciousness caused by postoperative hydrocephalus, posterior fossa edema, surgical site hematoma, brainstem infarction, and meningitis are independent predictors of PPCs in neurosurgical patients [8, 9]. PPCs have adverse impacts on prognosis, including an increased ICU occupancy rate, prolonged hospital stay, perioperative mortality, and increased hospitalization costs for non-cardiothoracic surgery patients [10–12].

Protective lung ventilation (PLV) strategies have been adopted by many anesthesiologists and are widely used in clinical anesthesia [13, 14]. A low tidal volume combined with positive end-expiratory pressure (PEEP) ventilation and an alveolar recruitment maneuver (ARM) are the most widely used PLV strategies and can reduce lung volume and pressure injuries, improve lung function, and reduce PPCs [15]. Intraoperative mechanical ventilation combined with PEEP has value in the prevention and treatment of postoperative atelectasis and other pulmonary complications, but the level of PEEP required among patients varies greatly. A single PEEP does not consider the individual differences between patients, which may affect the effect of PLV. If PEEP is too low, atelectasis cannot be prevented. If PEEP is too high, a lung pressure injury might occur and the thoracic pressure will be increased which together will be unfavorable with respect to blood reflux, thus affecting circulation stability [16, 17]. For patients undergoing craniotomy, PEEP may also affect intracranial pressure (ICP) and brain-blood reflux, affecting the surgical process and patient recovery.

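### The 24% and 13.5% behind the sample size cannot be incidences observed in a pilot of 20 patients per group, so the stated basis for 216 per group and 80% power is invalid as written

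*Protocol article*

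**What the plan says.** The section on sample size estimation and interim analysis in the protocol article names a pilot with 20 cases per group as the source of the planning rates. The complication rate found there at one week is reported as follows: "in the P6 and Pi groups was 24% and 13.5%, respectively". It continues "Using the PASS15.0 procedure with *α* = 0.05 and *β* = 0.2", and concludes that "the minimum sample size of each group was calculated to be 216 cases". Allowing for 20% dropout, it divides 216 by 0.8 to get 270 per group, and states that "A total of 540 patients will need to be enrolled in the two groups".

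The section on primary and secondary outcomes defines the incidence as the number of patients with a pulmonary complication divided by the number of patients in the group. The article offers no other origin for the two rates: no published control rate is used in the calculation, and no smallest worthwhile difference is given.

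**The concern.** Under the article's own definition, an incidence in a group of 20 is a whole number divided by 20. Neither 24% nor 13.5% has that form. Both are nevertheless reported as pilot observations, and together they fix the assumed effect of 10.5 points.

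The two rates carry the whole justification of the trial's size. If the pilot size is wrong, the evidence behind the rates is not what the reader is told. If the rates are wrong, 216 per group was computed for an effect that the pilot did not show. The reader cannot tell which, so cannot judge whether 80% power is a reasonable claim. Any report that repeats this justification would repeat the error.

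**Working it through.** **Inputs**, all from the sample size section unless noted: 20 per group in the pilot; rates 0.24 (P6) and 0.135 (Pi); α = 0.05; β = 0.2; 216 per group; dropout 20%; total 540. Allocation is 1:1 (Randomization section). Sidedness is not stated; two-sided is assumed because it reproduces the plan's figure.

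**1. Reproduce the plan's figure.** Pooled two-proportion formula without continuity correction:

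n = [1.960·√(2p̄(1−p̄)) + 0.8416·√(p1(1−p1) + p2(1−p2))]² / (p1 − p2)²

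- p̄ = (0.24 + 0.135)/2 = 0.1875, so 2p̄(1−p̄) = 0.3047
- p1(1−p1) + p2(1−p2) = 0.1824 + 0.1168 = 0.2992
- n = (1.0819 + 0.4603)² / 0.105² = 2.3784 / 0.011025 = 215.7, so **216**
- Power at 216 per group: 80.05%
- 216/0.8 = 270 per group; 2 × 270 = 540

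The calculation reproduces exactly, so the printed rates are the ones that were used. Other two-sided variants give 213 (unpooled), 214 (arcsine) and 235 (continuity correction); the one-sided version gives 170.

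**2. Test the rates against 20 per group.**

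- 0.24 × 20 = 4.8 patients
- 0.135 × 20 = 2.7 patients
- Possible values nearby: 2/20 = 10%, 3/20 = 15%, 4/20 = 20%, 5/20 = 25%. None rounds to 24% or 13.5%.

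**3. Test whether losses in the pilot explain it.** Suppose fewer than 20 were assessed in a group. For P6, 4/17 = 23.5% could be printed as 24%. For Pi, no denominator up to 20 gives 13.5%; the closest is 2/15 = 13.3%. The smallest denominator that gives 13.5% to one decimal is 37 (5/37). At least the Pi rate therefore cannot come from 20 or fewer patients.

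**4. See what possible pilot results would imply.** Same formula, two-sided 0.05, 80% power:

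| Pilot counts (P6 v Pi) | Rates | n per group | Power at 216 |
|---|---|---|---|
| 5/20 v 3/20 (nearest) | 25% v 15% | 250 | 74% |
| 4/20 v 2/20 | 20% v 10% | 199 | 83% |
| 4/20 v 3/20 | 20% v 15% | 906 | 28% |
| 5/20 v 2/20 | 25% v 10% | 100 | 99% |

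One patient more or fewer in the Pi group moves the requirement between 199 and 906. For the nearest pair, the 95% confidence interval of the difference (Newcombe) runs from about −15 to +34 points.

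**The case against.** The strongest reply is that this is a fault of reporting, not of design. Given 24% and 13.5%, the sample size is right and the power is 80%. Power depends on the true rates in the trial population, not on the pilot counts, and a pilot of 20 per group says little about those rates whatever its counts were. Allocation, outcome, analysis and type I error are untouched. All of that stands. It limits the consequence but does not remove the contradiction: the article presents the rates as observed in a stated number of patients, and they cannot have been. Nor is this a detail left to a fuller document, since the denominator and the rates are both printed here and are incompatible.

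A reader might infer that the trial is underpowered. The documents do not support that: of the four neighbouring results, two give more than 80% power at 216 and two give less.

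A reader might also set the 24% against the 39% incidence in the Introduction and conclude that the control rate is too low. That figure is general background and not an input to the calculation, and the trial's entry criteria select lower-risk patients (ASA I–II, age 18–65, no chronic lung disease). The direction of any effect on power also depends on what is held fixed. At a 39% control rate, the same 10.5-point reduction needs about 318 per group (64% power at 216). The same relative risk, 13.5/24 = 0.5625, gives 39% v 21.9% and needs 114 (97% power).

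**Conclusion.** The concern holds as a contradiction between the pilot's stated size and its stated results. Rates of 24% and 13.5% would need 4.8 and 2.7 patients out of 20, and no group of 20 or fewer gives 13.5%. Either the pilot size or the rates are misstated; the article does not show which. The only stated basis for 216 per group and 80% power is therefore invalid as written.

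The arithmetic that follows from the rates is sound, and the finding does not establish that 216 is too few. Results possible with 20 per group imply anything from 100 to 906 per group, or 99% down to 28% power at 216. These figures assume a two-sided pooled test without continuity correction and treat each possible pilot result as if it were the truth. They show how much hangs on the unreported counts; they do not estimate the trial's actual power.

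The impossibility itself rests only on the article's definition of incidence and on whole numbers of patients.

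**What to change.** Correct the sample size paragraph in one of two ways.

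1. State the true pilot counts and the denominator of each group, then restate the power of 216 evaluable patients per group at those rates.
2. Relabel 24% and 13.5% as planning assumptions, justify the 10.5-point difference, and state the 80% power as conditional on those two rates.

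In either case, state that the test is two-sided, since that is the version that yields 216.

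The cost is a paragraph of protocol text. The enrolment target of 540 need not change. The downside is that the stated power may become less favourable once the true counts are given.

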#### Statistics

Data will be collected in a standardized form and transmitted to the Data Monitoring Committee whenever the patient is discharged from the hospital. The completeness and the quality of the data will be checked by a data collector from the Data Monitoring Committee. Logical checks will be performed for missing data and to find inconsistencies. When necessary, the data collector will contact the investigator by phone to validate the data or reformat the data before entry into the database.

The SPSS 21.0 software package will be used for statistical analysis. The counting data will be expressed as the number of patients (percentage) and be analyzed using the chi-square (*χ*^2^) test or Fisher exact test. The normally distributed quantitative variables will be expressed as the mean ± standard deviation (SD). Two independent sample *t*-tests will be used for comparison between groups, and analysis of variance (ANOVA) will be used for comparison at different time points within the groups. Quantitative variables of the skewness distribution will be expressed as the median (interquartile range [IQR]) or mean (95% confidence interval [CI]), and the Mann-Whitney *U* test will be used for comparison. *P* < 0.05 will indicate that the difference is statistically significant. Intention-to-treat will be considered for the patients with an incomplete follow-up period. Missing values will be handled by the mixed model for repeated measurements.

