EIT-guided PEEP titration is a PEEP titration strategy that has attracted much attention in recent years. EIT images show the percentage of collapse and overexpanded areas corresponding to different PEEP levels in the total ventilation area, from which a curve of the percentage of collapse and overexpanded area can be drawn. The PEEP corresponding to the intersection of the two curves facilitates alveolar re-expansion as much as possible, while minimizing overexpansion, and thus, it is determined as the best PEEP. In the pre-experiments, the median PEEP obtained by EIT was 6 cmH_2_O. Therefore, we compare Pi with P6.

Considering that PEEP may increase thoracic pressure, affect hemodynamic stability, further increase intracranial pressure, affect cerebral perfusion, and have an impact on rScO_2_, we have chosen to apply PEEP for mechanical ventilation from the beginning of dura suturing to the end of the surgical procedure and before extubation to avoid its impact on the key stage of surgery. The doses of vasoactive drugs, PaO_2_/FiO_2_, and regional brain oxygen saturation will be used as observation indices to clarify the effectiveness and safety of individualized PEEP. Studies have shown that in patients with severe and acute brain injuries, the application of PEEP has no effect on intracranial pressure (ICP) or cerebral perfusion pressure (CPP) for those without severe lung injuries [39]. The increase in intracranial pressure is modest over the range of applied PEEP values (0–25 cmH_2_O), suggesting that PEEP may be safely applied to most mechanically ventilated patients with severe brain injuries. Therefore, we believe that it is relatively safe to titrate individualized PEEP in the range of 0–10 cmH_2_O. The purpose of this study is to explore the application value of pulmonary electrical impedance-guided individualized PEEP in reducing pulmonary complications within 1 week after a craniotomy. If it can be demonstrated that individualized PEEP reduces the incidence and severity score of pulmonary complications within 1 week after a craniotomy, showing a statistical difference or clinical significance, the study will promote the wide application of individualized PEEP in clinical anesthesia, further improve the prognosis of neurosurgical patients, and reduce the cost of hospitalization.

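### The protocol allows withdrawal from the trial after intraoperative events that PEEP may cause, without securing day-7 follow-up or analysis as randomised, so the primary comparison can be biased in either direction

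*Protocol article*

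**What the plan says.** Under Sample size estimation and interim analysis, the protocol article states: "we will consider patients withdrawal from the trial if the following conditions occur. (1) severe brain swelling during surgery". The second condition listed is persistent hypotension with circulatory instability. The exit named is from the trial, not only from the assigned ventilation. Withdrawal of research gives a further, open route: where participation is judged not to be in the patient's interest, "the researcher has the right to terminate his/her participation at any time".

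The article links both conditions to PEEP. The Introduction says that PEEP during craniotomy may lead to swelling of brain tissue. The Discussion says that "PEEP may increase thoracic pressure, affect hemodynamic stability, further increase intracranial pressure, affect cerebral perfusion".

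On analysis, the Statistics section says: "Intention-to-treat will be considered for the patients with an incomplete follow-up period". It then names a mixed model for repeated measurements for missing values. The primary outcome is whether any pulmonary complication occurs within 1 week, assessed daily to day 7. As a count variable it falls under the chi-square or Fisher test.

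**The concern.** The arms differ in the PEEP used from dura suturing to extubation, and the anaesthesiologist knows the allocation (Randomization section). If an event that PEEP can bring about leads to withdrawal from the trial, the share leaving may differ by arm. Patients with such an event may also have a pulmonary risk unlike that of the rest. Dropping them would then compare two groups that randomisation no longer makes alike.

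The article's safeguards do not close this gap. Saying that intention-to-treat will be considered is not a commitment to analyse everyone as randomised, and no analysis recovers outcomes that were not collected. A mixed model for repeated measurements can serve the outcomes measured at T0 to T3, such as the lung ultrasound score, but not one yes/no result per patient. At stake is the validity of the primary comparison.

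**Working it through.** **1. The plan's own figure.** Inputs from Sample size estimation and interim analysis: incidence "in the P6 and Pi groups was 24% and 13.5%, respectively", α = 0.05, power 0.80. Mean rate p̄ = (0.24 + 0.135)/2 = 0.1875. Two-sided test, pooled variance under the null, no continuity correction:

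n = [1.96·√(2·p̄·(1 − p̄)) + 0.8416·√(0.24·0.76 + 0.135·0.865)]² / 0.105² = 215.7, so 216 per group.

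This matches the article, and 216/0.80 = 270 matches too. The allowance leaves room for 270 − 216 = 54 patients per group without an outcome, for any reason.

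**2. When the conditions can depend on the arm.** Both arms have PEEP 0 from intubation to dura suturing, then the same recruitment manoeuvre and the same steps from 0 to 10 cmH2O. Only afterwards does one arm have 6 cmH2O and the other the individualised level. Swelling or hypotension before that point cannot be due to the allocated PEEP. From then until extubation it can be.

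**3. Size of the bias.** Let p be the true incidence in all randomised patients of an arm, w the share withdrawn and r the incidence in those withdrawn. Among those who remain,

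observed incidence = (p − w·r)/(1 − w).

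Take no true effect, p = 0.24 in both arms, 270 randomised per arm, and 270·(1 − w) analysed. The values of w and r are assumptions; the article gives none. The rejection probability is for the two-sided pooled z-test at 0.05.

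| Withdrawn P6 / Pi | r | Observed P6 | Observed Pi | P6 − Pi (points) | Rejection |
|---|---|---|---|---|---|
| 10% / 10% | 50% | 21.1% | 21.1% | 0 | 5.0% |
| 5% / 15% | 24% | 24.0% | 24.0% | 0 | 5.0% |
| 2% / 4% | 50% | 23.5% | 22.9% | 0.55 | 5.3% |
| 5% / 15% | 40% | 23.2% | 21.2% | 2.0 | 8.2% |
| 5% / 15% | 50% | 22.6% | 19.4% | 3.2 | about 14% |
| 10% / 20% | 50% | 21.1% | 17.5% | 3.6 | about 16% |
| 15% / 5% | 50% | 19.4% | 22.6% | −3.2 | about 14% |

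Example, fifth row: P6 (0.24 − 0.05·0.5)/0.95 = 0.215/0.95 = 22.6%; Pi (0.24 − 0.15·0.5)/0.85 = 0.165/0.85 = 19.4%. The last row swaps the arms: same size, opposite sign.

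**4. How far the planned result could move.** With the planned rates in 216 per arm (52 v 29 events), the uncorrected chi-square gives p = 0.005. Suppose that all 54 per arm allowed for were lost and are then restored, with 13 events (24%) among those lost in P6. Significance at 0.05 is lost once 18 of the 54 in Pi (33%) had a complication: 65/270 v 47/270, p = 0.056. This is an outer case, because the article does not tie the 20% to the two withdrawal conditions.

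**5. After the change.** At 24% v 13.5%, power is 80.0% with 216 per arm and 88.0% with all 270 per arm analysed.

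**The case against.** The strongest reply is that the article states less than a reader might infer.

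- **Withdrawal and loss of outcome.** A reader might infer that these patients are withdrawn and their day-7 outcome is not collected. The text says only that withdrawal will be considered, and nowhere that assessment stops. The primary-outcome formula divides by the total number in the group. Loss is inferred from the words on leaving the trial and from silence on continued follow-up. This stands. Analysis sets can also be left to an analysis plan, but the withdrawal rule is stated here, and a later analysis plan cannot supply outcomes that were never recorded.
- **Cause.** Allocated PEEP differs only from dura suturing onward. The Discussion judges titration over 0 to 10 cmH2O relatively safe, and the exclusion of intracranial hypertension and abnormal cardiac function should make the events rarer. This limits the window and probably the frequency; it does not remove the link.
- **Direction.** A reader might infer a false benefit for individualised PEEP. The article does not support that: individualised PEEP may lie above or below 6 cmH2O, and its pre-test median is 6.
- **Size.** With small differences in withdrawal the effect is slight, as the 2% v 4% row shows.
- **Safety.** A reader might infer that harm is hidden. The article requires the severity and causality of adverse events to be assessed and recorded, and the reasons for leaving to be entered in the case report form. The harm to guard against is in the efficacy comparison.

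**Conclusion.** The point holds in a limited form. For events after the allocated PEEP begins, the stated rule permits loss of the primary outcome that may depend on both arm and pulmonary risk, and the analysis text does not guard against it. The bias can go either way. In the cases shown it runs from none (equal withdrawal with equal risk, or withdrawn patients at average risk), through 0.55 points and 5.3% rejection, to 3.6 points and about 16%. These figures rest on assumed withdrawal shares and risks, on no true effect at 24%, and on withdrawn patients being left out. They show what the rule allows and do not forecast what will happen. That the withdrawals account for part of the 20% shedding rate is also only an inference; the article does not say so.

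**What to change.** Four changes of wording:

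1. State that patients who meet either condition remain in the trial for all pulmonary assessments and radiographs to day 7 unless they withdraw consent, whatever the clinical handling. That handling is not addressed here.
2. Replace the intention-to-treat sentence with: *The primary analysis includes all randomised patients in the arm assigned.*
3. Report these events, and all withdrawals with reasons, by arm.
4. Keep the mixed model for repeated continuous measurements, and for the primary outcome add a sensitivity analysis suited to a missing binary result, such as a tipping-point analysis over assumed risks in each arm.

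The cost is small: a protocol amendment, and continued assessment to day 7 of patients already under the trial team's observation. Keeping patients whose treatment departed from the assigned PEEP may dilute the effect slightly. No larger sample is needed: if the 10.5-point difference holds in all randomised patients, power is 88% with 270 per arm, against 80% with 216.
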